##### Anxiety symptoms

Anxiety symptoms as a separate construct will be assessed with the Dutch translation of the 69-item Screen for Child Anxiety Related Disorders (SCARED; Dutch version) [73, 74]. The SCARED-NL assesses anxiety disorders according to the DSM-IV in children aged 7 to 19 years [73]. All items are rated on a 3-point Likert scale. The SCARED has demonstrated a high internal consistency, good test–retest reliability, and adequate construct and predictive validity [74, 75]. Additionally, the SCARED – Parent Version will be used to assess anxiety symptoms according to the parent (SCARED-P) [74]. The SCARED-P consists of 69 items rated on a 3-point Likert scale, and shows good psychometrics [74].

##### Diagnosis of depression and anxiety

he presence of a current diagnosis of depression and/or anxiety at T2 will be assessed with the MINI (KID) (version 7.02) [55, 56]. The MINI is a structured, clinician-administered diagnostic interview that is widely used to assess the presence of psychiatric disorders based on the Diagnostic and Statistical Manual of Mental Disorders (Fifth edition; DSM-5) and the International Classification of Diseases (Tenth revision; ICD-10). For adolescents aged 13–17, sections A, B, D, E, F, G, H, U of the MINI KID will be administered. For adolescents aged 18 or 19 years, sections A, AY, B, E, D, F, FA, and N of the MINI will be administered. Both the MINI and MINI KID are well-validated, reliable interviews [54, 55, 76].

#####  Emotion regulation

Emotion regulation will be measured with two questionnaires: the Dutch translation of *Der Fragebogen zur Erhebung der Emotionsregulation bei Kindern und Jugendlichen* (FEEL-KJ: Duth version) [77, 78] and the Difficulties in Emotion Regulation Scale (DERS) [79]. The FEEL-KJ is a 90-item questionnaire that assesses 15 emotion regulation strategies (i.e., problem solving, distraction, forgetting, acceptance, humor enhancement, cognitive problem solving, revaluation, giving up, withdrawal, rumination, self-devaluation, aggressive actions, social support, expression, and emotional control) in response to anger, anxiety, and sadness in children and adolescents aged 10–19 years. All items are rated on a five-point Likert scale ranging from never to almost always. The primary emotion regulation strategies are divided into two secondary scales: the adaptive and maladaptive emotion regulation scale. Total scores on the secondary FEEL-KJ scales (adaptive and maladaptive scale) will be used. The FEEL-KJ is a reliable and valid instrument to measure emotion regulation in youth [77, 80].

The 36-item DERS assesses emotion regulation difficulties across six dimensions: non-acceptance of emotional responses, difficulty in engaging in goal-directed behavior, difficulty in controlling impulses, lack of emotional awareness, limited access to emotion regulation strategies, and lack of emotional clarity [79]. For each item, respondents rate how often they engage in different behaviors or have certain feelings on a 5-point Likert scale. Total DERS scores will be used, with higher DERS scores reflecting more emotion regulation difficulties [79]. The DERS was originally developed for adults, but has demonstrated high reliability and adequate validity for adolescents [81, 82] and is widely used in adolescent-research (e.g., [25]).

##### Global functioning, symptom severity and improvement

To asses global functioning of the adolescents, the CBT-therapist of the adolescent will fill in the Children’s Global Assessment Scale (CGAS) [83]. Adolescents are rated on a scale from 1 (extremely impaired) to 100 (superior functioning). To measure symptom severity and improvement the Clinical Global Impression Scales will be used (CGI) [84]. The CGI-Severity (CGI-S) is a 7-item scale ranging from a score of 1 (not ill) to 7 (requires inpatient care). The CGI-Improvement (CGI-I) is a 7-item scale that compares ratings of severity with previous measures, with scores ranging from 1 (very much improved) to 7 (very much worse). Both the CGAS and the CGI are widely used measures [83, 85].

#### Other variables of interest

##### Adolescent measures

In addition, other variables of interest that will be assessed in adolescents are:

Socio-demographics, collected at baseline.Intervention uptake of CBT, registered by the CBT therapist.Perceived impact of COVID-19, as measured with a self-developed COVID-19 questionnaire. See supplementary file 1 for an English translation of this questionnaire.Alcohol use, as measured with the Alcohol Use Disorders Identification Test (AUDIT) [86].Life events, as measured with a self-developed Life Events Questionnaire. See supplementary file 2 for an English translation of this questionnaire. This questionnaire is based on the Clinician-Administered PTSD scale for children and adolescents (CAPS-CA) and the Life Events Checklist [87, 88].Quality of the parent–child relation, as measured with the parent scale of the Inventory of Parent and Peer Attachment short form (IPPA-s) [89, 90].Self-esteem, as measured with the Rosenberg Self-Esteem Scale (RSES) [91].Sleep reduction, as measured with the Sleep Reduction Screening Questionnaire and additional sleep diary questions (SRSQ) [92].

##### Adolescents in the E-TRAIN group

Intervention uptake of E-TRAIN, measured through log data of the online platform.Treatment satisfaction, as measured with a modified version of the Client Satisfaction Questionnaire (CSQ-8) [93].

##### Parent/ caregiver measures

Additional parent/ caregiver measures that will be assessed are:

Socio-demographics of the parent, collected at baseline.Emotion regulation of the child of adolescent?, as measured with the FEEL-KJ – Parent Report (FEEL-KJ: Parent Report) [78, 94].Parental? Coping with the adolescent’s negative emotions, as measured with the Coping with Children’s Negative Emotions Scale – Adolescent Version (CCNES-A) [95].Emotion dysregulation of the parent, as measured with the Difficulties in Emotion Regulation Scale (DERS) [79].Psychiatric distress of the parent, as measured with the Brief Symptom Inventory – short version (BSI-18) [96].

##### Therapist measures

The CBT therapist of each participant will be asked to report the following: number of CBT sessions, content and number of sessions of non-CBT care. Additionally, the E-TRAIN therapist will be asked to fill in an adapted version of the System Usability Scale to measure the usability of the online intervention (SUS) [97].

### Data analyses

#### Primary outcome measures

Linear mixed models will be used to determine the effectiveness of adding E-TRAIN to CBT in reducing depressive and anxiety symptoms (measured with the RCADS25). A two-level structure will be used (Level 1: repeated measures, Level 2: patients). The overall treatment effect will first be evaluated in a model with condition and the baseline value of the outcome. Second, between-group differences at each time-point will be examined by adding time and the interaction of time and condition to the model. Time will be treated as a categorical variable, represented by dummy variables. Furthermore, as a sensitivity analysis, we will fit a model adjusted for the total number of completed CBT sessions and other potentially relevant confounders. Imputation of missing data will not be necessary because we will use mixed-model analyses, which adequately handles missing values [98]. Analyses will be conducted on the entire randomized sample (i.e. intention to treat) and on the per protocol/treatment completers sample. For the treatment completers sample of the experimental (E-TRAIN) condition, adolescents who completed ≥ 66% of the online sessions (four sessions or more) will be regarded as completers. The aforementioned main analyses will also be conducted separately for those with a primary diagnosis of depressive disorder, and for those with a primary diagnosis of anxiety disorder. Analyses will be conducted using SPSS version 26 + and R version 3.0 + . Statistical significance will be set at α < 0.05.

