#### Focus groups

Additionally, we will organize two focus groups to evaluate the experimental intervention. We aim to include six randomly selected participants for each focus group. Adolescents who participate in the focus group will receive a voucher of 25 euros. Focus groups will take approximately 1.5 h, and will be led by a psychologist and a researcher. In addition, we will organize a focus group with a random sample of six E-TRAIN therapists to examine the acceptability of the internet-based emotion regulation training.

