**Fig. 2 Fig2:**
[figure not shown]
Summary of E-TRAIN sessions

Additional to these six online sessions, E-TRAIN consists of three video conference sessions with a therapist. At the start of E-TRAIN, a video conference session of 30 min will be scheduled. This video conference session will be held in order to acquaint patients with their therapist and vice versa, and to determine E-TRAIN treatment goals. After finishing the first three online sessions, a second video conference session will be scheduled to provide guidance and monitor the patient's progress. At the end of E-TRAIN, a final video conference session will be scheduled. In this session, the treatment goals will be evaluated and the focus will be on applying the learned emotion regulation skills in daily life.

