#### E-TRAIN therapists

Patients will be guided by a psychologist who has been trained in the application of E-TRAIN. After each online session, these E-TRAIN therapists will provide feedback and guidance using secured messages within the online platform. To ensure treatment integrity, E-TRAIN therapists will receive a detailed treatment protocol with standardized feedback templates. E-TRAIN will take place simultaneously to CBT, and will start after the first 2–4 CBT sessions. Based on the patient’s preference, the six sessions of E-TRAIN will be completed on either a weekly or fortnightly schedule; hence, E-TRAIN will be completed in 6 to 12 weeks. All adolescents will be guided by an E-TRAIN therapist other than their CBT therapist.

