#### Treatment as usual: CBT

Both groups will receive CBT, a commonly used evidence-based therapy for adolescents with anxiety [61] and depression [62, 63]. CBT will be provided by experienced MSc or registered Health Care psychologists. The primary goal of CBT is to identify and restructure maladaptive thought patterns and behaviors (e.g., [64, 65]). Key components of CBT for adolescents with depressive and anxiety disorders are 1) psychoeducation; 2) behavioral activation, exposure, and behavioral experiments; 3) cognitive restructuring; and 4) relapse prevention [65, 66].

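### The primary mixed model has no term for E-TRAIN therapist, who clusters patients in the experimental arm only, so the standard error may be too small

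*Protocol article*

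**What the plan says.** Under Data analyses, Primary outcome measures, the protocol article names the levels of the model: "A two-level structure will be used (Level 1: repeated measures, Level 2: patients". On the fixed terms it says: "The overall treatment effect will first be evaluated in a model with condition and the baseline value of the outcome". Time and its interaction with condition are added in a second step. The one sensitivity analysis named adjusts for the number of CBT sessions completed and other possible confounders; it does not deal with clustering. The Secondary outcome measures section carries the same procedures over to the secondary outcomes.

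The intervention sections describe a further grouping. The E-TRAIN therapists section says: "Patients will be guided by a psychologist who has been trained in the application of E-TRAIN", and adds: "All adolescents will be guided by an E-TRAIN therapist other than their CBT therapist". These therapists respond in writing after every online session, of which there are six. The E-TRAIN section adds personal contact: "E-TRAIN consists of three video conference sessions with a therapist". CBT is common to both arms (Treatment as usual: CBT): "Both groups will receive CBT, a commonly used evidence-based therapy for adolescents with anxiety".

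The number of E-TRAIN therapists is not stated. The Focus groups section bears on it: "we will organize a focus group with a random sample of six E-TRAIN therapists". The Sample size section gives 69 patients per arm, including 35% extra for drop-out, and mentions no allowance for clustering.

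**The concern.** Patients are randomised individually, but after randomisation those in the experimental arm are gathered into the caseloads of E-TRAIN therapists. With some 69 patients and a modest number of therapists, several patients share one therapist. If therapists differ in how well their patients do, outcomes within a caseload are correlated. This happens in one arm only, a partially nested design.

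The therapist component then enters the variance of the experimental-arm mean, and so the treatment contrast, as variance between caseloads. A model with measurements within patients treats it as independent patient-level noise. The reported standard error is then too small, the confidence interval too narrow and the test at 0.05 too liberal. For the interval this holds whatever the true mean effect is.

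This is not a detail that the article leaves open for an analysis plan: the two levels are stated positively. The omission also passes to the secondary outcomes.

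**Working it through.** The plan has no clustering figure to reproduce, so the check asks what the omission does over a stated range of assumptions.

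**Inputs from the protocol**
- 69 per arm, 1:1 allocation, with 35% extra for drop-out (Sample size, Randomization). Undoing the inflation gives 69 / 1.35 = 51 analysed per arm.
- At least 6 E-TRAIN therapists (Focus groups), so on average at most 69 / 6 = 11.5 patients each.
- Two-sided test at 0.05.

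**Assumptions not in the protocol**
- ICC among patients of one E-TRAIN therapist: 0.01 to 0.10.
- Number of therapists K: 6 or 10.
- Equal caseloads, and equal total variance in the two arms.

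**Formulas**
- Mean caseload: m = n / K
- Design effect in the E-TRAIN arm: DE = 1 + (m − 1) × ICC
- True over reported standard error: R = √((1 + DE) / 2), because only one of the two arms is inflated
- True type I error: 2 × (1 − Φ(1.96 / R))

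**Worked case:** n = 51, K = 6, ICC = 0.05. m = 8.5; DE = 1 + 7.5 × 0.05 = 1.375; R = √(2.375 / 2) = 1.090; 1.96 / 1.090 = 1.80; type I error 7.2%.

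The last column is a simulation of a baseline-adjusted comparison at one follow-up that ignores therapist (8,000 runs per row). It stands in for the T2 contrast of the planned model.

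| n per arm | K | m | ICC | DE | R | Type I error | Simulated |
|---|---|---|---|---|---|---|---|
| 51 | 10 | 5.1 | 0.02 | 1.082 | 1.020 | 5.5% | 5.8% |
| 51 | 10 | 5.1 | 0.05 | 1.205 | 1.050 | 6.2% | 5.9% |
| 51 | 10 | 5.1 | 0.10 | 1.410 | 1.098 | 7.4% | 7.4% |
| 51 | 6 | 8.5 | 0.02 | 1.150 | 1.037 | 5.9% | 6.1% |
| 51 | 6 | 8.5 | 0.05 | 1.375 | 1.090 | 7.2% | 6.7% |
| 51 | 6 | 8.5 | 0.10 | 1.750 | 1.173 | 9.5% | 9.4% |
| 69 | 10 | 6.9 | 0.01 | 1.059 | 1.015 | 5.3% | 5.2% |
| 69 | 10 | 6.9 | 0.05 | 1.295 | 1.071 | 6.7% | 6.6% |
| 69 | 6 | 11.5 | 0.01 | 1.105 | 1.026 | 5.6% | 5.6% |
| 69 | 6 | 11.5 | 0.02 | 1.210 | 1.051 | 6.2% | 6.6% |
| 69 | 6 | 11.5 | 0.05 | 1.525 | 1.124 | 8.1% | 7.8% |
| 69 | 6 | 11.5 | 0.10 | 2.050 | 1.235 | 11.3% | 11.7% |

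At ICC 0 the simulated error is 4.8% to 5.2%. With many therapists the problem fades: for K = 23 and 69 per arm the formula gives 5.1% to 6.2% over ICC 0.01 to 0.10.

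**Offset.** The planned model also names no term for the stratification factors (diagnosis, site) or for CBT therapist. Their effects are shared by both arms, so leaving them out makes the standard error too large. Adding both to the simulation, each at an assumed 5% of variance, with 69 per arm:

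| K | ICC 0 | ICC 0.02 | ICC 0.05 |
|---|---|---|---|
| 6 | 4.0% | 5.1% | 7.0% |
| 10 | 4.0% | 4.8% | 5.8% |

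This simulation gave both arms equal numbers of patients per CBT therapist. Stratifying by diagnosis and site does not guarantee that, so these figures favour the offset.

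**The case against.** **The ICC may be small.** Therapist input is limited to written feedback and three video sessions, beside full CBT in both arms, and it is standardised: "E-TRAIN therapists will receive a detailed treatment protocol with standardized feedback templates". This stands as a reason to doubt values near 0.10, which nothing in the documents supports. It is no reason to fix the ICC at zero: templates cover the written feedback, while the video sessions are individual.

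**A reader might infer that type I error certainly exceeds 5%.** The documents do not support that. It needs a positive ICC, which they do not give. If E-TRAIN did nothing through any therapist, the therapist variance would be zero and the error would stay at 5%; inflation needs a zero mean effect together with differences between therapists. Even with a positive ICC, the shared-effect omissions can cancel the inflation, as they do at ICC 0.02 with 10 therapists (4.8%). Still, two omissions that may happen to cancel are not a justification for the model.

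**A reader might infer that the error favours E-TRAIN.** It does not. The estimate is not biased, and a two-sided test with too small a standard error gives false positives equally in both directions.

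**A reader might try fewer than six therapists to get larger figures.** Drawing six at random for a focus group implies at least six and suggests more. K = 6 is therefore the adverse end of the range, not its middle.

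**The remedy has limits.** With few therapists the variance component is poorly estimated and may come out at zero, and small-sample degrees of freedom may cost power. This stands, and it is why the change is proposed as a sensitivity analysis and not as a replacement of the primary model.

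**Conclusion.** The point holds in conditional form. The stated two-level model omits a grouping that exists in the experimental arm only, and neither the model nor its one named sensitivity analysis allows for it. If outcomes vary between E-TRAIN therapists, this omission taken alone makes the standard error of the treatment contrast too small.

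The size rests on an assumed ICC, therapist count and equal caseloads. With 6 to 10 therapists:
- 51 analysed per arm, ICC 0.02 to 0.05: type I error about 5.5% to 7.2%, true standard error 2% to 9% above the reported one.
- 69 analysed per arm, ICC 0.01 to 0.05: about 5.3% to 8.1%.
- ICC 0.10 with 6 therapists, an upper end without support in the documents: 9.5% with 51 per arm, the true standard error being 17% above the reported one, and 11.3% with 69 per arm.

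These figures come before any offset from omitted strata and CBT-therapist effects, which could remove the inflation when the ICC is small. The documents do not show that the trial's test is in fact too liberal, nor that the primary model has to be replaced. They do show a plausible gap that is cheap to guard against.

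**What to change.** Add to Data analyses, Primary outcome measures, wording such as: *As a pre-specified sensitivity analysis, the T2 between-group difference will be re-estimated in a partially nested mixed model that adds a random intercept for E-TRAIN therapist in the CBT + E-TRAIN arm only, with Satterthwaite or Kenward-Roger degrees of freedom. The number of E-TRAIN therapists, their caseloads and the estimated therapist ICC will be reported.*

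Record each patient's E-TRAIN therapist as a study variable. The sites will presumably know it, but the article mentions platform log data only for intervention uptake and does not say that therapist identity is captured.

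The cost is about two sentences of text, one recorded variable and one variance parameter, with no further patient assessments. The interval will be somewhat wider, and with few therapists the ICC will be imprecise. If the therapist variance is estimated at zero, the result should lie close to that of the planned model.

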**Methods:**

In this multicenter two-arm randomized controlled trial with parallel group design, we aim to include 138 adolescents, aged 13–19 years, referred for treatment and diagnosed with depressive and/or anxiety disorder. Participants will be allocated to either CBT or CBT + E-TRAIN. Assessments will take place at baseline, and at 3 (T1), 6 (T2) and 12 (T3) months after baseline. We will conduct multi-informant assessments: the adolescent, a parent/caregiver, and the CBT therapist will be asked to fill in questionnaires. The continuous primary outcome measure is self-reported depressive and anxiety symptoms at six months after baseline, measured with the RCADS25. Secondary outcome measures include anxiety or depression diagnosis based on a semi-structured clinical interview, emotion (dys) regulation, and parent-report measures of anxiety, depression and emotion (dys) regulation.

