## Methods

### Design

To determine the effectiveness of adding E-TRAIN to CBT, we will conduct a multicenter two-arm randomized controlled trial (RCT) using a two-arm parallel group design. We aim to include 138 adolescents with a primary diagnosis of depressive and/or anxiety disorder. After completion of baseline assessment (T0), participants will be allocated to either CBT or CBT + E-TRAIN. Follow-up assessments will take place after 3 (T1), 6 (T2: primary outcome), and 12 months (T3) post-baseline assessment. See Fig. 1 for the trial flowchart. All assessments are online questionnaires, which will be completed by multiple informants (adolescents, parents/caregivers, and therapists), except for the Mini (KID) International Neuropsychiatric Interview (MINI version 7.02) [54, 55], which will be assessed in a telephone interview 6 months after baseline. This protocol was written in accordance with the Standard Protocol Items: Recommendations for Interventional Trials (SPIRIT) guideline [56]. This study has been registered in the Netherlands Trial Register (NL9564). The Medical Research Ethics Committees United (MEC-U) in the Netherlands has approved the study protocol.

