### Sample size

We will conduct a pairwise comparison between the treatment arms (CBT + E-TRAIN vs. CBT). The continuous primary outcome measures will be depressive and anxiety symptoms at T2. A priori sample size calculation was performed using the *sampsi* command in Stata (version 14.0; Stata Corp, College Station, USA). We aim to include *N* = 138 adolescents (*n* = 69 in each group) to be able to detect a Cohen’s d of 0.40 with α = 0.05 (two-sided) and power = 0.80, taking into account 35% extra inclusion to account for drop-out.

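### The primary outcome is RCADS25 at 6 months, but the primary analysis leads with an effect averaged over 3, 6 and 12 months and does not say which result decides the trial

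*Protocol article*

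**What the plan says.** Three places in the protocol article fix the primary time point at 6 months.

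- Abstract, Methods: "The continuous primary outcome measure is self-reported depressive and anxiety symptoms at six months after baseline, measured with the RCADS25".
- Methods, Design: "Follow-up assessments will take place after 3 (T1), 6 (T2: primary outcome), and 12 months (T3) post-baseline assessment".
- Methods, Sample size: "The continuous primary outcome measures will be depressive and anxiety symptoms at T2".

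Data analyses, Primary outcome measures, specifies a linear mixed model with repeated measures nested in patients. Its first step is: "The overall treatment effect will first be evaluated in a model with condition and the baseline value of the outcome". Its next step is: "Second, between-group differences at each time-point will be examined by adding time and the interaction of time and condition to the model". Time is categorical. One significance level of 0.05 is given, with no ranking of the two steps or of the time points. Table 1 schedules the RCADS25 at T0, T1, T2 and T3. The Secondary outcome measures paragraph applies the same procedure to the secondary outcomes.

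**The concern.** The endpoint is a difference at one time point, while the first test listed for it is an average over the follow-up. These are different estimands. They coincide only if the treatment effect is the same at every visit, and the protocol gives no reason to assume that. E-TRAIN runs alongside CBT after the first 2–4 CBT sessions ("hence, E-TRAIN will be completed in 6 to 12 weeks"), so T1 may fall close to the end of training, and T3 is six months beyond the endpoint.

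At stake is what counts as the trial's result. If the averaged effect and the T2 effect point in different directions on significance, the analysis section gives no rule for which one answers the primary question. A choice made after seeing the data would not hold the 5% error rate.

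**Working it through.** **1. What the first model estimates.** Baseline is a covariate, so the outcomes are the RCADS25 at T1, T2 and T3. With no time term and no interaction, there is one condition coefficient: a weighted mean of the three visit-specific differences. The article does not say that it pools 3, 6 and 12 months. This follows from the model terms and Table 1, and I see no other reading that fits.

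**2. Whether the sample size settles which test was meant.** It does not. The stated inputs (d = 0.40, two-sided 0.05, power 0.80) give 2 × ((1.960 + 0.842)/0.40)² = 98.1, so 99 per arm before drop-out, not 69. The figure 69 can be reached with correlations that the article does not state, and from either estimand:

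- T2 alone, adjusted for baseline with r = 0.7: factor 1 − 0.49 = 0.51.
- Mean of three follow-ups, with correlation 0.3 to baseline and 0.4 between follow-ups: factor (1 + 2 × 0.4)/3 − 0.09 = 0.51.

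Both give 98.1 × 0.51 = 50.04, so 51, and 51 × 1.35 = 68.9, so 69. The sample size is a separate matter and this point does not rest on it.

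**3. How far the two tests can differ.** From the article: 69 per arm, two-sided 0.05. Assumed, because the article gives none: unit SD, all correlations 0.5, cumulative drop-out of 12%, 20% and 26% at T1, T2 and T3, and the effect profiles.

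After baseline adjustment, each visit has variance 1 − 0.25 = 0.75 and each pair of visits covariance 0.5 − 0.25 = 0.25. Generalised least squares over the drop-out patterns gives the pooled coefficient weights of 0.379, 0.326 and 0.296 on T1, T2 and T3 and a standard error of 0.120. The T2 contrast has a standard error of 0.164. Power is Φ(effect/SE − 1.960); the opposite tail is negligible or, in the weakest case, about 0.1%.

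Worked example, 0/0.40/0.20 SD:

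- Pooled effect = 0.326 × 0.40 + 0.296 × 0.20 = 0.189; 0.189/0.1203 = 1.57; power Φ(−0.39) = 35%.
- T2 = 0.40/0.164 = 2.44; power Φ(0.48) = 68%.

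| Assumed effect at T1/T2/T3 (SD) | Pooled effect | Power, pooled | Power, T2 |
|---|---|---|---|
| 0 / 0.40 / 0.20 | 0.19 | 35% | 68% |
| 0.20 / 0.40 / 0.30 | 0.29 | 69% | 68% |
| 0.40 / 0.40 / 0.40 | 0.40 | 91% | 68% |
| 0.50 / 0.20 / 0.40 | 0.37 | 87% | 23% |

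The pooled test can miss an effect present at T2, do as well as the T2 test, do better, or succeed when the effect at the declared endpoint is small.

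**4. Type I error if either test could be claimed.** Under the same settings the two statistics correlate at 0.73, and under the null at least one is significant in 8.2% of trials. Without drop-out and with correlations of 0.5 to 0.7, the figure is about 8.0%. Independent tests would give 1 − 0.95² = 9.75%. With T2 alone it is 5%.

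**The case against.** The strongest reply is that T2 is named as primary three times and the T2 contrast is estimated in the second model, so a fair reader would take T2 as decisive. The words first and second may describe only the order of model building. No passage calls the overall effect primary or confirmatory, and a condensed article may leave the ranking of tests to the full protocol or analysis plan. Much of this stands. No estimate is missing, and the gap is one of designation. What remains is a conflict within the text shown: the section headed as the primary-outcome analysis opens with a test that does not match the declared endpoint, and nothing there links back to T2.

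Four stronger readings are tempting, and the document does not support them.

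- **That nothing makes T2 decisive, or that two tests are set up as co-primary.** The endpoint declarations favour T2, and no second test is labelled primary.
- **That the plan's error rate is 8%.** That figure holds only if success could be claimed on either test, and the article states no such rule.
- **That the pooled test loses power.** This depends on the profile. With milder dilution the two tests are about equal, and with a constant effect the pooled test is clearly stronger.
- **That many adolescents are still in training at T1.** If CBT is weekly and starts at baseline (an assumption), weekly users finish around weeks 8 to 10 (2–4 plus 6), before T1 at about week 13. Fortnightly users finish around weeks 14 to 16 (2–4 plus 12). The mix of schedules is not given.

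**Conclusion.** The point holds as a mismatch between the declared endpoint and the lead analysis. The primary outcome is the RCADS25 at T2, but the first test is of an average over T1, T2 and T3, the T2 difference is one of three unranked contrasts, and the section does not say which result decides the trial. This conclusion rests on the text and needs no assumption about effect sizes.

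The practical size does need assumptions. In the scenarios above, pooled power ranges from 35% to 91%, against 68% for T2 where the T2 effect is 0.40 SD; for 0.50/0.20/0.40 it is 87% against 23%. The type I error of about 8% is conditional on either result being claimable. The profiles, correlations and drop-out rates are illustrative and do not come from the article.

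**What to change.** In Data analyses, Primary outcome measures, state that the single confirmatory test is the between-group difference in RCADS25 at T2, from the planned model with baseline, categorical time, condition and time × condition, at two-sided 0.05. Report the overall effect and the T1 and T3 contrasts as secondary estimates with confidence intervals.

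Make the change before the outcome data are analysed. An unblinding date cannot serve as the anchor, because the Randomization section provides for blinding only of the T2 diagnostic interviewers.

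The cost is about two sentences, with no new data and no new model. The downside is power: if the effect is constant over time, the T2 contrast is weaker than the pooled test (68% against 91% at 0.40 SD under the settings above). It is, however, the endpoint that the protocol already declares.
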